# Effects of Oliceridine Versus Sufentanil on Postoperative Recovery Quality During Hysteroscopy Under Laryngeal Mask Airway Anesthesia: Protocol for a Single-Blind and Randomized Controlled Trial

**DOI:** 10.2196/84521

**Published:** 2026-01-02

**Keywords:** oliceridine, hysteroscopy, quality of recovery, opioid-related adverse events, sufentanil, general anesthesia

## Abstract

**Background:**

Hysteroscopy, the gold standard for diagnosing and treating intrauterine pathologies, has shown substantial increase in its adoption in clinical practice. Nevertheless, early postoperative pain and opioid-related adverse effects remain critical determinants of recovery quality. Oliceridine—a novel G protein-biased μ-opioid receptor agonist—demonstrates an improved therapeutic range over conventional opioids in preliminary studies.

**Objective:**

This study aims to evaluate whether oliceridine enhances recovery quality while reducing opioid-related complications compared to sufentanil in patients undergoing hysteroscopy under general anesthesia.

**Methods:**

This single-center randomized controlled trial will enroll 120 patients undergoing hysteroscopy under general anesthesia with 1:1 randomization to sufentanil- or oliceridine-based analgesia. The primary outcome is early recovery quality assessed by the 15-item Quality of Recovery scale at 24 hours after the surgery, while secondary outcomes include hemodynamic fluctuations during induction, total intraoperative opioid consumption and supplemental bolus frequency, proportion requiring vasoactive agents, incidence of respiratory depression in postanesthesia care unit, postoperative extubation time, opioid-related adverse events within 24 hours, and Visual Analog Scale pain scores at 30 minutes, 4 hours, 8 hours, and 24 hours postextubation.

**Results:**

This study received approval from the Medical Ethics Committee of Deyang People’s Hospital, Deyang, China, on April 16, 2025 (approval 2025-03-009-K01). Participant recruitment is anticipated to be completed by December 2025. Data analysis, manuscript preparation, and submission for publication are expected to be completed by February 2026.

**Conclusions:**

The successful completion of this trial will generate evidence regarding whether oliceridine enhances recovery quality while reducing opioid-related complications compared to sufentanil in patients undergoing hysteroscopy under general anesthesia.

**Trial Registration:**

Chinese Clinical Trial Registry ChiCTR2500104024; https://www.chictr.org.cn/showproj.html?proj=275501

**International Registered Report Identifier (IRRID):**

DERR1-10.2196/84521

## Introduction

Hysteroscopy is currently recognized as the gold standard for diagnosing and treating intrauterine pathologies, having revolutionized gynecological diagnostics and operative interventions. This modality enables both diagnostic evaluations and surgical treatments through a minimally invasive approach, characterized by rapid postoperative recovery. Advancements in hysteroscopic technologies and instrumentation have substantially increased its adoption across diverse patient populations [1,2]. Pain remains a leading cause of procedural failure during hysteroscopy. To optimize surgical conditions and enhance satisfaction for both patients and surgeons, hysteroscopic procedures in China are predominantly performed under general anesthesia. A nationwide survey revealed that 63.8% of the hysteroscopic surgeries used anesthesia in 2021, underscoring its critical role in contemporary practice [3]. European data corroborate this pattern, with a retrospective analysis confirming that a proportion of hysteroscopic procedures also necessitate general anesthesia for successful completion [4].

To date, no robust evidence exists to define optimal anesthesia protocols for pain management in hysteroscopy, and standardized approaches remain underexplored. For hysteroscopic procedures anticipated to be lengthy or involving significant tissue trauma, the 2020 Chinese Expert Consensus on Anesthesia Management recommends general anesthesia with laryngeal mask airway (LMA) to ensure procedural tolerance [5]. Current clinical practice predominantly uses conventional opioids such as sufentanil for intraoperative analgesia. However, sufentanil administration is associated with multiple opioid-related adverse effects, including nausea, vomiting, excessive sedation, respiratory depression, drug dependence, and opioid-induced hyperalgesia, which collectively compromise early postoperative recovery [6].

Oliceridine is a novel G protein-biased μ-opioid receptor agonist that selectively activates G protein signaling while minimizing β-arrestin recruitment. This pharmacological profile confers a mechanistic advantage: selectively engaging intracellular analgesic pathways while avoiding those mediating adverse effects [7,8]. As such, oliceridine has garnered emerging clinical interest for hysteroscopic analgesia.

The 15-item Quality of Recovery scale (QoR-15) is a multidimensional construct evaluating patient-centered recovery, encompassing physical, physiological, psychological, social, and functional domains [9,10]. The QoR-15—validated for reliability and clinical utility—quantifies recovery across 5 dimensions: physical comfort, emotional status, psychological support, independence, and pain experience. Postoperative pain intensity, nausea/vomiting incidence, and opioid consumption profiles constitute key determinants of patient recovery quality [11,12].

Therefore, this study uses QoR-15 as the primary endpoint to evaluate oliceridine's efficacy within LMA-based general anesthesia for hysteroscopy. We aim to determine whether oliceridine enhances recovery quality while reducing opioid-related complications compared to sufentanil in patients undergoing hysteroscopy under general anesthesia.

## Methods

### Study Design

This prospective, single-center, single-blind, randomized controlled study will be conducted at Deyang People's Hospital, Deyang, China. The protocol received ethical approval from the institutional ethics committee (2025-03-K01) and was registered at the Chinese Clinical Trial Registry on June 10, 2025. Written informed consent will be obtained from all participants or their legal guardians. Eligible patients will be randomly allocated to either the sufentanil (S) group or oliceridine (O) group. The participant recruitment timeline is shown in Figure 1. A time schedule for the enrollment, interventions, and assessments is detailed in Table 1.

**Figure 1 figure1:**
[figure not shown]
Flowchart for this study.

**Table 1 table1:** The study schedule of the enrollment, interventions, and assessments.

Timepoint		Enrollment phase (day 1)	Allocation (before surgery)	Surgery (during anesthesia)	Follow-up (within 24 h after surgery)
**Enrollment**					
	Eligibility screening	✓			
	Informed consent	✓			
	Allocation		✓		
**Interventions**					
	Sufentanil			✓	
	Oliceridine			✓	
**Assessments**					
	Baseline data	✓			
	Primary outcome				✓
	Secondary outcome			✓	✓

### Eligibility Criteria

Inclusion criteria are as follows: (1) patients scheduled for hysteroscopic surgery under LMA general anesthesia who were assessed by physicians as unable to tolerate the pain stimuli associated with surgical manipulation, (2) patients aged 18 to 65 years, (3) patients with American Society of Anesthesiologists physical status I-III, and (4) patients who voluntarily sign informed consent.

Exclusion criteria are as follows: (1) patients with American Society of Anesthesiologists physical status IV or higher (indicating severe systemic disease, functional incapacity, including but not limited to New York Heart Association class III or higher heart failure, myocardial ischemia, severe reduction in cardiac ejection fraction, third-degree atrioventricular block, stage 3 hypertension, respiratory failure, severe chronic obstructive pulmonary disease, severe pulmonary dysfunction, or decompensated hepatic or renal insufficiency); (2) patients with known allergy to any component of the investigational drugs or contraindications to their use; (3) patients unable to cooperate (eg, psychiatric disorders, anticipated difficulty with neuropsychological assessment, or communication barriers due to pronunciation or dialect); (4) patients with a history of alcohol or substance abuse; (5) patients with concurrent participation or participation in another clinical trial within 12 weeks prior to this trial; (6) patients with BMI>30 kg/m²; (7) patients unable to comprehend the study procedures or refusal to participate; and (8) patients with any condition deemed by the investigator to pose an unacceptable risk or to contraindicate participation, such as anticipated difficult airway management.

### Randomization and Blinding

Block randomization with block sizes of 4 or 6 will be performed using a computer-generated sequence. An independent researcher not involved in the trial will prepare sequentially numbered, opaque, sealed envelopes containing group assignments. Participants will be allocated in a 1:1 ratio to either the experimental or control group by opening these envelopes in a sequential order at the time of enrollment. Allocation cards will be sealed inside opaque envelopes to ensure concealment. The study medications (oliceridine or sufentanil) will be prepared by a dedicated research nurse as visually identical clear solutions in 10-mL syringes. These prepared syringes will then be provided to the anesthesiologist, who will remain unaware of the treatment allocation. Blinding will be maintained for the participants, the anesthesiologist, and the outcome assessors throughout the trial to minimize assessment bias. The blinding will be broken only in the event of severe adverse events. Study participants, their legally authorized representatives, the anesthesiologist, and outcome assessors will be blinded to group allocation throughout the trial. Unblinding the allocation is generally not required per protocol. Emergency unblinding will be performed exclusively to determine rescue medications for critical adverse events or during other medical emergencies

### Interventions

#### Explanation for the Choice of Comparators

This study evaluates the impact of oliceridine (group O) on early postoperative recovery quality in patients undergoing hysteroscopic surgery under general anesthesia. The sufentanil-based regimen (group S) serves as the comparator because of its status as the conventional analgesic approach for such procedures in current clinical practice.

Both groups will receive identical anesthesia induction and maintenance protocols but with divergent analgesic regimens. Group O will be administered oliceridine at a dose of 60 μg/kg (diluted to 10 mL with normal saline) as a slow intravenous bolus for induction. Supplemental doses of 30 μg/kg will be provided if intraoperative analgesia is deemed inadequate, defined as mean arterial pressure and/or heart rate exceeding 20% above baseline values. Group S will receive sufentanil at a dose of 0.3 μg/kg (similarly diluted to 10 mL) as an induction bolus, with supplemental doses of 0.15 μg/kg administered under the same hemodynamic criteria.

#### Anesthesia Protocol

Upon arrival in the operating room, standard monitoring, including pulse oximetry, invasive radial arterial blood pressure, and electrocardiography will be initiated. Thirty minutes prior to induction, the attending anesthesiologist will administer intravenous penehyclidine hydrochloride (0.01 mg/kg) and ondansetron (4 mg). Anesthesia induction will begin with a slow intravenous bolus of either sufentanil or oliceridine according to group assignment. One minute later, propofol (2 mg/kg) and cisatracurium (0.15 mg/kg) will be administered. After satisfactory neuromuscular blockade is achieved, an LMA will be inserted. Mechanical ventilation will be initiated with a tidal volume of 6-8 mL/kg predicted body weight and positive end-expiratory pressure of 5 cmH₂O. Anesthesia will be maintained using a continuous infusion of propofol (4-12 mg/kg/h), with supplemental opioids administered based on hemodynamic criteria (mean arterial pressure or heart rate >20% above baseline). The propofol infusion rate will be titrated to maintain a bispectral index value between 40 and 60. Neuromuscular blockade will be maintained with intermittent boluses of cisatracurium (one-third of the induction dose). If reversal is required, neostigmine (0.02 mg/kg) and atropine (0.01 mg/kg) will be administered. After surgery, all patients will be transferred to the postanesthesia care unit.

#### Criteria for Discontinuing or Modifying Allocated Interventions

The criteria for discontinuing are as follows: (1) severe anesthesia/surgical complications (eg, anaphylaxis, shock, cardiac arrest, malignant arrhythmias, aspiration requiring intervention, malignant hyperthermia), (2) protocol deviation in anesthesia/surgical technique, (3) withdrawal of consent, (4) anticipated difficult airway, and (5) failed LMA placement.

#### Strategies to Improve Adherence to Interventions

The principal investigator will conduct preoperative evaluations against inclusion/exclusion criteria one day prior to surgery. During informed consent, the investigator will detail the study procedures to participants and legally authorized representatives, outlining participant responsibilities.

#### Relevant Concomitant Care Permitted or Prohibited During the Trial

The provision of additional care during the trial followed institutional protocols.

### Outcomes

The primary outcome is defined as the quality of postoperative recovery at 24 hours after surgery and will be assessed using QoR-15 (score range: 0-150; higher scores indicate better recovery). Secondary efficacy endpoints are (1) hemodynamic changes during induction (mean arterial pressure/heart rate at T0 [pre-drug], T1 [pre-LMA], T2 [post-LMA immediate], T3 [5-min post-LMA]); (2) total intraoperative opioid consumption and supplemental bolus frequency; (3) proportion requiring vasoactive agents; (4) incidence of postanesthesia care unit respiratory depression (defined as respiratory rate <6 bpm, end-tidal carbon dioxide amplitude change >50 mm Hg or <30 mm Hg, or waveform loss >20 s); (5) time to extubation; (6) opioid-related adverse events within 24 hours; and (7) Visual Analog Scale pain scores at 30 minutes, 4 hours, 8 hours, and 24 hours postextubation.

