### Data Collection and Management

Baseline data will include demographic characteristics (age, sex, BMI), the preoperative QoR-15 score, and comorbidities with diagnostic verification. Intraoperative records will include vital signs, anesthetic agents/dosages, surgical duration, and proportion requiring vasopressor administration. In the postanesthesia care unit, time to extubation, early postoperative Visual Analog Scale pain scores, and incidence of respiratory depression will be documented. Postoperative recovery quality will be assessed at 24 hours by using QoR-15, with 24-hour adverse events systematically recorded. Predefined subgroup analyses stratified by age will be conducted for primary and secondary outcomes, applying identical statistical approaches as specified for the main analyses.

Source data will be documented using standardized case report forms. To minimize data entry errors, independent dual-entry verification will be performed. Physical records will be stored securely in locked cabinets with restricted access within the Department of Anesthesiology. Electronic data will be hosted on encrypted, cloud-based platforms.

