### Statistical Analysis

The primary analysis will be conducted on a modified intention-to-treat population, defined as all randomized participants who receive the study drug (oliceridine or sufentanil) at anesthesia induction. The per-protocol population will consist of modified intention-to-treat participants who complete the 24-hour follow-up assessment without major protocol deviations, serving as the population for supportive analyses. All participants who receive the study drug will be included in the safety analysis set.

Primary/secondary outcomes will be analyzed using SPSS software (version 27.0; IBM Corp), with continuous variables first assessed for normality via Kolmogorov-Smirnov testing; normally distributed data will be expressed as mean (SD), nonnormal data as median (IQR), and categorical variables as counts (%). Quantitative between-group comparisons will employ independent-samples *t* tests or Mann-Whitney *U* tests, while qualitative comparisons will use chi-square, continuity-corrected chi-square, or Fisher exact tests, with all tests being 2-tailed (statistical significance threshold: *P*<.05).

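### The planned tests for mean arterial pressure and heart rate do not use the pre-drug (T0) value as a covariate, and the plan does not say how T0 enters the analysis

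*Protocol article*

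**What the plan says.** Protocol article, Outcomes: the first secondary endpoint is "hemodynamic changes during induction (mean arterial pressure/heart rate at T0 [pre-drug], T1 [pre-LMA], T2 [post-LMA immediate], T3 [5-min post-LMA". T0 is therefore one of the endpoint's listed measurement times. The endpoint is named as a change, but no change score or other summary is defined.

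Protocol article, Statistical Analysis: the section covers primary and secondary outcomes alike ("Primary/secondary outcomes will be analyzed using SPSS software (version 27.0; IBM Corp"). Its rule for continuous data is "Quantitative between-group comparisons will employ independent-samples *t* tests or Mann-Whitney *U* tests", chosen after a normality check and "with all tests being 2-tailed (statistical significance threshold: *P*<.05". No covariate or repeated-measures model is named.

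Protocol article, Data Collection and Management: the same rule carries over to the age subgroups ("Predefined subgroup analyses stratified by age will be conducted for primary and secondary outcomes, applying identical statistical approaches as specified for the main analyses"). The baseline list reads "Baseline data will include demographic characteristics (age, sex, BMI), the preoperative QoR-15 score, and comorbidities with diagnostic verification"; it contains no preoperative pain score. The pain endpoint is "Visual Analog Scale pain scores at 30 minutes, 4 hours, 8 hours, and 24 hours postextubation", so all four of its times follow treatment.

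**The concern.** A two-sample test takes one number per patient, but MAP and HR each supply four. The plan does not say how the four become one. The natural reading is a comparison at each time, possibly including T0. A between-group test at T0 would say nothing about the drug, because T0 precedes it. The other reading is that T0 is subtracted from each later value.

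On neither reading does T0 serve as a covariate, although it is measured in every patient and is likely to predict T1 to T3. What is at stake is the precision of the haemodynamic comparison, and a clear statement of what is being compared.

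**Working it through.** **Figures in the plan.** The document gives no variance, correlation or power for MAP or HR. Its only calculation is the sample size for the 15-item Quality of Recovery scale (QoR-15), which does not bear on this point. There is no plan figure to reproduce here.

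**Step 1: the two readings.**
- Time by time: 2 variables × 4 times = 8 comparisons, 2 of them at T0.
- Change from T0: 2 variables × 3 times = 6 comparisons, none at T0.

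Both fit the Outcomes and Statistical Analysis sections. Neither uses T0 as a covariate.

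**Step 2: inputs.** From the Sample Size section: 60 per group. Assumed: correlation r between T0 and a later value of 0.3, 0.5 or 0.7; equal variance at T0 and later and in both groups; a linear relation. The figures refer to the t-test branch of the rule.

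**Step 3: variance of the between-group comparison, relative to a raw post-dose value.**
- Raw post-dose value: 1
- Change from T0: 2(1 − r)
- Adjusted for T0 (ANCOVA): 1 − r²
- Adjusted relative to change: (1 − r²) / [2(1 − r)] = (1 + r)/2

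| r | Raw | Change | Adjusted | Cut vs raw | Cut vs change |
|---|---|---|---|---|---|
| 0.3 | 1 | 1.40 | 0.91 | 9% | 1 − 0.65 = 35% |
| 0.5 | 1 | 1.00 | 0.75 | 25% | 1 − 0.75 = 25% |
| 0.7 | 1 | 0.60 | 0.51 | 49% | 1 − 0.85 = 15% |

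Adjustment has the smallest variance in every row. Below r = 0.5 a change score is worse than ignoring T0. The percentages do not depend on the sample size.

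**Step 4: what this means for power.** Assume a true effect of 0.5 SD, 60 per group and two-sided 0.05. Power = Φ(0.5 / (s × √(2/60)) − 1.96), where s is the square root of the variance in the table and √(2/60) = 0.1826. For raw values, 0.5/0.1826 = 2.739, and Φ(0.779) gives 78%.

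| r | Raw | Change | Adjusted |
|---|---|---|---|
| 0.3 | 78% | 64% | 82% |
| 0.5 | 78% | 78% | 89% |
| 0.7 | 78% | 94% | 97% |

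**Step 5: type I error.** Over all randomizations each unadjusted test keeps its 5% error. Given a particular T0 imbalance, the raw-value test does not. An imbalance of 0.3 SD is 0.3/0.1826 = 1.64 standard errors, and one at least that large arises in about 10% of trials. At 0.3 SD the conditional false-positive rate of a raw post-dose test is 6.7%, 9.5% and 12.8% for r = 0.3, 0.5 and 0.7. Lower rates in well-balanced trials offset this. It is the same loss of precision seen from another side, and it applies only if raw values are compared.

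**The case against.** The strongest defence is that the text is a general rule by variable type in a condensed article, and that models for secondary endpoints are often left to an analysis plan that is not shown. The endpoint is called a change, and T0 is the obvious reference for one, so a t test on change from T0 fits both sections. This stands to a degree: the document does not settle which reading is meant. It does not remove the point, because a method is stated for these outcomes and it has no covariate on either reading.

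Four stronger inferences are tempting, and the documents do not support them.

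- **That the plan tests the groups at T0.** T0 is listed as a measurement time. No sentence says it is compared between groups.
- **That the false-positive rate is inflated.** The conditional rates in Step 5 hold only at a given imbalance. Unconditionally the rate is 5% per test.
- **That there are 12 separate tests (8 for MAP and HR, 4 for pain) with a 34% to 41% chance of at least one false positive at within-series correlation 0.7 to 0.5.** This assumes separate testing at every time, including T0, and pools three independent variables. The document does not state separate testing, and it presents no secondary result as confirmatory.
- **That the pain scores suffer the same fault.** All four pain times are postextubation and no baseline pain score is listed, so there is nothing to adjust for.

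It is also fair to say that one overall test per variable is not clearly better. Before, just after and five minutes after mask insertion are distinct moments, and effects of opposite sign could cancel. Time-specific contrasts are legitimate, and the fix keeps them.

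**Conclusion.** The point holds for MAP and HR only. The stated method leaves a measured pre-drug value unused as a covariate, and the role of T0 in the endpoint is undefined. The loss is small to large depending on an unknown correlation: from r = 0.3 to 0.7, adjustment would cut variance by 9% to 49% against raw values, or by 35% to 15% against change scores. These figures rest on equal variances and a linear relation. The endpoint is secondary, so the QoR-15 analysis and its error rate are untouched. This is a worthwhile and nearly free improvement, not a threat to the trial's validity. The four pain-score comparisons need no change of model on this account and should be read as exploratory secondary results.

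**What to change.** In the Statistical Analysis section, state that:

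- MAP and HR at T1, T2 and T3 are each analysed with the patient's T0 value as covariate, either by ANCOVA at each time or by one mixed model per variable with group, time, group-by-time and T0 terms;
- adjusted group differences at each time are reported with 95% confidence intervals;
- T0 is summarised by group without a P value;
- the normality-based choice between t and Mann-Whitney tests does not apply to these two variables;
- the pain-score comparisons at the four times are exploratory.

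The age-subgroup analyses follow automatically, since they reuse the main methods.

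The cost is a few sentences. T0 is already being recorded, and the sample size does not change. Recruitment is under way and analysis is expected in the first quarter of 2026, so the wording should be fixed and dated before anyone examines unblinded data.
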